## Study Measures

**Study Outcomes**

This analysis will evaluate how the values and trends in the following outcomes changed since the onset of the COVID-19 pandemic:

1. Body Mass Index - (to be calculated from most height and weight and/or measures independently entered as BMI).
2. Height to derive BMI – most recent adult height will be used, even if this was recorded prior to the study period.
3. Weight – all weights during the study periods will be recorded.
4. Systolic and Diastolic Blood Pressure (Home and Clinic readings).
5. Lipid profile: Total cholesterol, LDL cholesterol, HDL cholesterol, triglycerides
6. HbA1c
7. Smoking status
8. Referral to a weight management programme

**Study Exposures**

This is a time series analysis that will compare values and trends pre-COVID to those following the onset of COVID (with the date 1^st^ March 2020 considered the onset of the COVID pandemic).

**Covariates**

Stratified analysis will be undertaken to assess the impact of the COVID pandemic based on variations in the following:

1. Age
2. Sex
3. Ethnicity recorded in primary care records or linked HES data.
4. Index of Multiple Deprivation (IMD)
5. Geographic Data
6. The presence of Comorbidities - existing and new diagnoses of Quality Outcomes Framework (QOF) conditions
   1. Atrial Fibrillation
   2. Coronary Heart Disease
   3. Heart Failure
   4. Hypertension
   5. Peripheral Arterial Disease
   6. Stroke and TIA
   7. Diabetes Mellitus
   8. Asthma
   9. Chronic Obstructive Pulmonary Disease
   10. Dementia
   11. Depression
   12. Mental Health
   13. Cancer
   14. Chronic Kidney Disease
   15. Epilepsy
   16. Learning Disabilities
   17. Osteoporosis
   18. Rheumatoid Arthritis
   19. Palliative Care
   20. Non diabetic hyperglycaemia
7. Date of registered live birth or still birth – to identify outcome data in the prenatal or postnatal periods which should be excluded from the analysis.

QOF conditions *have been included as a covariate, to identify whether patients living with specific comorbidities such have experienced greater need for targeted weight loss interventions. We have chosen to look at comorbidities covered by QOF as these have been benchmarked as common and/or important by NICE, and are likely to be well-coded in the EHR.*

## Study Duration

Outcome data will be collected over the following time periods:

Pre-covid period: 1^st^ March 2015- 1^st^ March 2020

This will be included to identify baseline levels of the outcomes in the population and underlying trends prior to the onset of the pandemic.

Post-covid period: 1^st^ March 2020 – point of data extraction

This will allow an assessment of how values and trends varied in the periods post covid compared to the pre-covid period

# STATISTICs and data analysis

1. Primary care data is entered by health care professionals into the Electronic Health Records (EHRs) as a combination of free text and clinical codes which specify specific diseases and disease processes. Best practice of record keeping is to ensure that clinical codes are entered in addition to free text so EHRs can be rapidly searched and reviewed for clinical, audit and research purposes. More than one code can be used to represent a single clinical condition or measurement, therefore ‘code lists’ are required to identify all the relevant information.
2. This analysis will be limited to data entered as clinical codes Specific code lists will be developed to identify data related to each of the study outcomes, exposures and covariates listed above. Where established code lists are available they will be reviewed and curated to ensure the data being collected are aligned with the specific analysis being performed. Such code lists may be available from previous studies researching the same conditions or aligned with care processes, such as the Quality Outcome Framework ( a national system of monitoring the quality of GP care processes in relation to common and important chronic diseases such as diabetes, hypertension and asthma).
3. Data will be analysed using STATA.
4. Descriptive statistics will be used to describe the numbers and character of the population who are having each of the outcome measures and how this varied in the period before and after the onset of the pandemic. This will help describe any bias introduced by different health care practices in the period before and after the pandemic in terms of which individuals were having the outcomes measures.
5. Changes in the values and trends of each of the outcomes listed above will be assess on a population level and individual level in time series analysis standardised for age and sex using an appropriate model based on the character of the data.
6. Further analyses will assess how population level trends in each of the outcomes have changed since the onset of the pandemic, after standardisation for age and sex, using an appropriate model based on the character of the data.
7. Multilevel modelling, accounting for clustering at the level of the Primary Care Network will be used to evaluate whether these outcomes varied by the demographic subgroups or comorbidities listed above.
8. Rates of referral to weight management programmes and variation by demographic groups and co-morbidity listed above will be assessed to identify current uptake of an intervention.
9. Missing exposure and covariate data (such as ethnicity) is likely to be Missing Not At Random. Missing data will be described and an assessment will be made whether to exclude individuals with missing for significant covariates such as ethnicity or IMD from the regression analyses, to consider those with missing values as a separate category or to use multiple imputation techniques.
10. To reduce the impact of pregnancy-associated changes on the analysis – outcome data entered in the six months before or after a live birth or still birth will be excluded from the analysis.

Data and all appropriate documentation will be stored for a minimum of 5 years after the completion of the study, including the follow-up period.

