## Risk of bias in the results

This analysis is using routinely collected data from electronic health record of patients attending their GP surgery. This is dependent on a patient being in contact with the GP surgery and the health care professional in the GP surgery measuring the outcome of interest (such as the patient’s BMI). As such, there are likely to be differences between people who have needed to attend their GP and have these outcomes measured compared to those who have not. Therefore we will need to be clear when we interpret and publish the data that the findings from this analysis may not represent that of the general population. Additionally we are assessing whether trends and values in the recorded BMI and metabolic parameters have changed since the onset of the pandemic, as access to care and care provision has changed during the pandemic, this could introduce further bias in terms of who is having these measures taken in the post pandemic period and whether changes seen in this group represent the wider population of patients attending their GP (but not having BMI or other metabolic parameters assessed). We will carefully explore these limitation in the conduct of the study (through assessing the numbers and characteristics of individuals who are having outcomes measured before and after the onset of the pandemic) and interpret the findings transparently to highlight the risk of any bias. However, this analysis will provide an indication for the need for weight loss interventions based on patients attending their GP. Furthermore, we hope the findings will inform further research.

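### Population trends are standardised for age and sex only, so a change in who is measured after March 2020 can appear as a change in BMI or metabolic risk

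*Protocol*

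**What the plan says.** All items cited are in the protocol section Statistics and data analysis unless another section is named.

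- **Adjustment set.** Item 5 assesses values and trends at "population level and individual level in time series analysis standardised for age and sex". Item 6 adds further population-level analyses of how the outcomes "have changed since the onset of the pandemic, after standardisation for age and sex". Both leave the model open, but both name the standardisation variables, and these are age and sex.
- **Expected bias.** The section Risk of bias in the results notes that access to care and its provision changed, and that "this could introduce further bias in terms of who is having these measures taken in the post pandemic period".
- **Planned response.** Item 4 describes who has each outcome measured: "This will help describe any bias introduced by different health care practices in the period before and after the pandemic". The bias section says the limitation will be explored "through assessing the numbers and characteristics of individuals who are having outcomes measured before and after the onset of the pandemic" and reported openly.
- **Other covariates.** The Covariates section lists ethnicity, IMD, geography and 20 QOF conditions. Their stated role is stratification: "Stratified analysis will be undertaken to assess the impact of the COVID pandemic based on variations in the following". Item 7 uses multilevel models, which "will be used to evaluate whether these outcomes varied by the demographic subgroups or comorbidities listed above".
- **Missing data.** Item 9 begins "Missing exposure and covariate data (such as ethnicity) is likely to be Missing Not At Random" and deals with exposures and covariates. It does not mention people whose outcome was not measured.

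**The concern.** An outcome enters the series only if the patient was in contact with the practice and someone took the measurement. Suppose routine measurement fell after March 2020 while monitoring of people with long-term conditions fell less. Those measured would then contain a larger share of people with such conditions at every age and in both sexes. If these people have higher BMI, HbA1c or blood pressure, the age-sex-standardised mean rises although nobody has changed. A shift the other way would hide a real rise.

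A table of who was measured lets the reader suspect this but leaves the estimated trend as it was. The Introduction says the findings will inform NHS England policy on how much need there is for weight loss interventions, and Objective 3 looks at both weight gain and prevalence of obesity. An artefact of measurement could therefore be read as need, or could mask it.

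**Working it through.** **The plan's own figure.** There is none. The protocol gives no BMI distribution, no measurement rates and no expected change. Every number below is an assumption chosen to show the mechanism and its range.

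**Set-up.** Within each age-sex cell, a share p of measured people has a given condition and the rest do not. Mean BMI differs by d between the two groups and is constant over time in each, so the true change is 0. Direct standardisation fixes the weights of the age-sex cells but leaves p free. If p shifts by the same amount in every cell:

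apparent change = (p after − p before) × d

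**Apparent change in standardised mean BMI (kg/m2), p before = 30%**

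| p after | d = 1 | d = 2 | d = 3 |
| --- | --- | --- | --- |
| 35% | 0.05 × 1 = 0.05 | 0.05 × 2 = 0.10 | 0.05 × 3 = 0.15 |
| 40% | 0.10 × 1 = 0.10 | 0.10 × 2 = 0.20 | 0.10 × 3 = 0.30 |
| 50% | 0.20 × 1 = 0.20 | 0.20 × 2 = 0.40 | 0.20 × 3 = 0.60 |

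The sign follows the shift. A 10-point fall in p with d = 2 gives −0.10 × 2 = −0.20.

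**Check with explicit cells.** Take six age-sex cells with:
- weights 0.15, 0.20, 0.15, 0.15, 0.20, 0.15;
- mean BMI without the condition 25, 27.5, 27, 26, 28.5, 28;
- p before 0.1, 0.3, 0.5, 0.1, 0.3, 0.5, and 0.1 higher in each cell after;
- d = 3.

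The weighted BMI without the condition is 27.1. The weighted p is 0.30 before and 0.40 after. The standardised means are 27.1 + 3 × 0.30 = 28.0 and 27.1 + 3 × 0.40 = 28.3, an apparent rise of 0.3 with no true change. Standardising also to a fixed p within each cell gives 28.0 both times, so the apparent change is 0.

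**Apparent prevalence of BMI above 30.** Assume normal BMI with means 27 and 30 and SD 5. The proportions above 30 are 1 − Φ(0.6) = 0.2743 and 0.5.
- p = 30%: 0.7 × 0.2743 + 0.3 × 0.5 = 34.2%
- p = 40%: 0.6 × 0.2743 + 0.4 × 0.5 = 36.5%
- p = 50%: 0.5 × 0.2743 + 0.5 × 0.5 = 38.7%

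**Limits of the illustration.** The shift in p must occur within age-sex cells; any part due to age or sex is already removed. The calculation shows only the effect of a shift in a recorded characteristic. If, within a recorded group, heavier people became more likely to be weighed, standardising for the condition would not remove that.

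**The case against.** The strongest reply is that the protocol is open about the bias and plans more than description. Item 5 includes an individual-level analysis, which largely avoids the mix problem if it compares people with themselves. The Covariates section stratifies by ethnicity, IMD, geography and QOF condition, and item 7 models the same factors. Within a diabetes stratum, a change in the share of people with diabetes has no effect at all. Weighting for measurement is also commonly left to an SAP, which is not shown here, and the bias section already warns that the findings may not represent the general population.

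Much of this stands, and a reader should not infer that the plan has no safeguards. Three things remain:
- The individual-level analysis is not tied to paired measurements, fixed windows or a pre-pandemic comparator.
- Stratifying by one factor leaves shifts in the others within each stratum, and neither the stratification nor item 7 is offered as a correction of the overall trend.
- The model is left open, but the standardisation set is not: the protocol itself fixes it at age and sex.

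On Objective 2 the objection is right in part. The programme named there is open to people with diabetes or hypertension, so a rising share of such people among those measured cannot drive eligibility within those groups. A reader might also infer that counts of eligible people must fall because fewer are weighed. That assumes raw counts of people currently measured, and the protocol does not say how the number will be derived.

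**Conclusion.** The point holds for the population-level trends in items 5 and 6. The protocol foresees that the measured population may change, fixes an adjustment set that cannot remove such a change within age-sex cells, and offers description in its place; unmeasured outcomes are not covered by item 9. On assumed inputs the artefact is about 0.05 to 0.6 kg/m2 in mean BMI. The true size and direction are unknown, because the documents give neither the shift nor the BMI gap.

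Three stronger readings are not supported:
- That the artefact *will* occur. The protocol says only that the bias could arise, and the arithmetic shows only that it can.
- That it matches any plausible pandemic effect. No figure in the documents allows that comparison.
- That it distorts a headline estimate. The protocol names no primary estimate, and targeting rests largely on comparisons between subgroups.

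This is a cheap and worthwhile improvement to an acknowledged limitation.

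**What to change.** **Main change, item 6.** Keep the age-sex series and report beside it a series standardised, or inverse-probability-weighted for being measured, on age, sex, QOF conditions fixed at the start of each interval, ethnicity, IMD, region and last prior BMI. All but the last are listed covariates, and prior BMI comes from the outcome records. The gap between the two series shows how much of the trend is due to recorded case mix.

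**Supporting analysis, item 5.** Specify the individual-level analysis as within-person change between a fixed pre-pandemic and a fixed post-onset window, set against within-person change over an interval of the same length before the pandemic. It should support the population series and not replace it, because people measured in both windows are themselves selected and the stated aim concerns adults living in the UK.

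**Objective 2.** Alongside any count, report the proportion eligible among those measured, applied to a fixed, named denominator.

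**Cost.** Protocol wording, additional modelling and some added variance, with no new data collection. Selection on BMI itself within recorded groups, and selection into being measured twice, would remain; the protocol should say so.

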## Study Population

Population size: The OpenSAFELY platform provides access to all patients registered with a GP surgery using TPP or EMIS Electronic Health Record software. A recent analysis in the OpenSAFELY platform demonstrated that gave access to 58 million patient records.(Walker, MacKenna et al. 2021)

Inclusion Criteria

1. Registration with a GP surgery, on the 1^st^ March 2020, that uses EMIS or TPP software to record and store electronic health records
2. All adults: aged >18 and <110 on the 1^st^ March 2020
3. Recorded female or male sex on the 1^st^ March 2020

Exclusion Criteria

1. Patients will less than 12 months primary care data available on the 1^st^ March 2020

(new registrations in the 12 months prior to 1^st^ March 2020 will be excluded from the analysis as there are often delays in the transfer of health records between practices).

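### Item 7 names only the Primary Care Network as a clustering level; with model-based standard errors, intervals may be too narrow for covariates that vary between practices within a network

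*Protocol*

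**What the plan says.** Item 7 of the Statistics and data analysis section sets the method for subgroup and comorbidity comparisons: "Multilevel modelling, accounting for clustering at the level of the Primary Care Network will be used" to judge whether outcomes differ by those characteristics. The Primary Care Network is the only level named anywhere in the Protocol. The Protocol gives neither the random-effects structure nor the type of standard error.

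Three other places point to the practice as the unit where data arise:

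- Study Population, first inclusion criterion: "Registration with a GP surgery, on the 1^st^ March 2020, that uses EMIS or TPP software".
- Statistics and data analysis, item 1: "Primary care data is entered by health care professionals into the Electronic Health Records (EHRs) as a combination of free text and clinical codes".
- Risk of bias in the results, which makes the data depend on the patient's contact with the surgery and on "the health care professional in the GP surgery measuring the outcome of interest".

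The covariates to be compared are age, sex, ethnicity, deprivation, geography and 20 Quality Outcomes Framework conditions.

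**The concern.** In a random-intercept model, correlation that is not given its own level goes into the residual, and the residual is assumed independent between patients. If the network is the lowest cluster in the model, two patients of one practice are treated as no more alike than two patients of different practices in the same network. For a covariate that is itself unevenly spread over those practices, the model counts more independent information than there is, and its standard error is too small.

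Ethnicity, deprivation and recorded comorbidity plausibly have that uneven spread. Geography has it only if it is recorded more finely than a network; a broad region hardly varies within one. Contrasts on these covariates feed Objective 1 (who gained more weight) and Objective 3 (which groups to target). Differences between groups could be reported as firmer than they are.

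**Working it through.** **No figure to reproduce.** The Protocol states no intraclass correlation (ICC), practice size, sample size or standard error for these models. What can be checked is the direction of the effect, and its size over a range of assumptions.

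**Assumed inputs (none from the Protocol).** Practices nest in networks, with m = 5 practices per network. Measured patients per practice n = 500 to 6,000. Outcome ICC at network level ru = 0.01 and at practice level rv = 0.01 to 0.03. Share of covariate variance between networks b = 0.02 and between practices within a network p = 0 to 0.10, with the rest w = 1 − b − p within practices. Balanced design, total outcome variance 1, s2 = 1 − ru − rv.

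**Formulas for a model with a network intercept only.**

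- Practice mean square: MSP = n·rv + s2
- Residual variance the model sees: MSW = [(m − 1)·MSP + m(n − 1)·s2] / (mn − 1)
- Network mean square: MSB = mn·ru + n·rv + s2
- Information: I = (p + w)/MSW + b/MSB
- Model variance = 1/I
- True variance = [(w·s2 + p·MSP)/MSW² + b/MSB] / I²
- R = √(model variance / true variance); actual coverage of a nominal 95% interval = 2Φ(1.96R) − 1

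**One case in full** (n = 2,000, rv = 0.01, p = 0.10, so w = 0.88 and s2 = 0.98).

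- MSP = 2,000 × 0.01 + 0.98 = 20.98
- MSW = (4 × 20.98 + 5 × 1,999 × 0.98)/9,999 = 0.988
- MSB = 10,000 × 0.01 + 20 + 0.98 = 120.98
- I = 0.98/0.988 + 0.02/120.98 = 0.992, so model variance = 1.008
- True variance = [(0.88 × 0.98 + 0.10 × 20.98)/0.988² + 0.0002]/0.992² = 3.08
- R = √(1.008/3.08) = 0.572 and coverage is 73.8%; the interval should be 1/0.572 = 1.75 times as wide

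The usual short formula agrees: 1 + (n − 1) × p × rv = 1 + 1,999 × 0.10 × 0.01 = 3.0, square root 1.73.

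**Over the range.** Mildest: n = 500, rv = 0.01. Severest: n = 6,000, rv = 0.03. Widening needed = 1/R.

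| Covariate variance between practices (p) | R, mildest (coverage) | R, severest (coverage) | Widening needed |
|---|---|---|---|
| 0 | 1.004 (95.1%) | 1.012 (95.3%) | none |
| 0.5% | 0.991 (94.8%) | 0.724 (84.4%) | 1.01 to 1.38 |
| 2% | 0.956 (93.9%) | 0.461 (63.4%) | 1.05 to 2.17 |
| 10% | 0.814 (89.0%) | 0.226 (34.2%) | 1.23 to 4.42 |

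**Do network-clustered robust standard errors repair it?** A simulation used 400 replicates, 100 networks, 5 practices each, 60 patients per practice, practice ICC 0.05, network ICC 0.01 and 5% of covariate variance between networks. The Monte Carlo error of a coverage near 95% is √(0.95 × 0.05/400), about 1.1 percentage points.

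| p | Empirical SE | Model SE (coverage) | Robust SE (coverage) |
|---|---|---|---|
| 0 | 0.0058 | 0.0059 (94.3%) | 0.0058 (94.5%) |
| 2% | 0.0059 | 0.0059 (96.3%) | 0.0060 (96.5%) |
| 10% | 0.0069 | 0.0059 (90.8%) | 0.0066 (93.3%) |
| 50% | 0.0101 | 0.0061 (76.3%) | 0.0095 (94.5%) |

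Robust errors at network level largely absorb the practice correlation.

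**Absolute scale.** As an illustration, assume 10 million measured adults, a BMI SD of 6 kg/m² and a subgroup of 10%. The independent-data half-width is 1.96 × 6 × √(1/1,000,000 + 1/9,000,000) = 0.012 kg/m². Three times that is 0.037 kg/m². A subgroup one hundredth that size (10,000 people) has a half-width of about 1.96 × 6/√10,000 = 0.12 kg/m², and three times that is 0.35 kg/m².

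**The case against.** The strongest reply is that item 7 has not fixed anything wrongly. It names a level without calling it the sole one, and it leaves the structure and the standard errors open. A statistical analysis plan, not shown here, may add the practice. One of the two remedies below, network-clustered robust errors, is already compatible with the sentence as written. This stands in part: a reader might infer that the Protocol rules out a practice level, and it does not. The point survives because the one level the Protocol does name sits above the level where its own text places registration and measurement.

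A reader might also infer that subgroup intervals in general will be too narrow. The documents do not support that. It takes both model-based standard errors and a covariate that varies between practices within a network; for a balanced covariate the standard error is right or about 1% too large.

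The sentence under Risk of bias concerns who gets measured. It does not say that BMI or HbA1c values correlate within a practice once the network is accounted for, so that correlation is an assumption here.

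Finally, a reader might infer that practice differences in referring will be mistaken for patient-group differences, and that referral must be compared within practices. That is a different question. Objective 4 asks whether groups differ in their likelihood of referral, and an overall difference can properly include differences between practices. Referral also has its own entry, item 8, which names no multilevel model, so it is unclear whether item 7 covers it.

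**Conclusion.** The point holds conditionally and is minor. A model with a network intercept only and model-based standard errors understates uncertainty for covariates that differ between practices within a network, and leaves other covariates alone. The understatement runs from about 1% to more than fourfold in interval width. That range rests wholly on assumed ICCs, practice sizes and covariate shares, and below a share of 0.5% the effect can vanish. For large subgroups the intervals stay narrow in absolute terms even after correction, so a changed conclusion is unlikely there. For small or strongly practice-clustered groups it could matter.

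**What to change.** In item 7, do one of the following:

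- add a random intercept for the practice of registration, nested within Primary Care Network; or
- keep the network effect and state that standard errors are cluster-robust at network level, which relies on practices nesting within networks.

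The cost is one sentence in the Protocol and, mainly for the extra level, longer run time on a very large data set. If a within-practice comparison of referral is wanted, add it as a secondary analysis beside the overall comparison, not in its place.

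### The pregnancy exclusion needs a recorded birth, so pregnancies still ongoing at extraction stay in the data and can add a small upward drift in weight at the end of the post-period only

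*Protocol*

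**What the plan says.** Three parts of the Protocol bear on this.

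- **The rule.** STATISTICs and data analysis, item 10: "outcome data entered in the six months before or after a live birth or still birth will be excluded from the analysis". Its aim is "To reduce the impact of pregnancy-associated changes on the analysis".
- **The trigger.** Covariates, item 7, lists one pregnancy variable: "Date of registered live birth or still birth". It is there "to identify outcome data in the prenatal or postnatal periods which should be excluded from the analysis". No code for a current pregnancy, booking visit or due date is listed.
- **The time frame.** 1 March 2020 is "considered the onset of the COVID pandemic" (Study Exposures). The post-period ends at the "point of data extraction" (Study Duration), with no run-off to let later births appear. Within both periods, "all weights during the study periods will be recorded" (Study Outcomes).

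**The concern.** The rule looks back from a birth, so it works only once the birth is on record. For readings taken late in the pre-period, the births fall after 1 March 2020 and can be seen. For readings taken late in the post-period, some births fall after extraction and cannot. The same rule therefore performs differently at the ends of the two periods being compared.

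Late-pregnancy weights, and the BMI values derived from them, then accumulate towards the end of the series. In a study of whether trends changed after March 2020, that can look like late weight gain in women of childbearing age. Objectives 1 and 3 ask which groups gained most, and item 5 of the statistics section also assesses change within individuals, where a late-pregnancy weight would count as personal gain. With access to records on the scale of 58 million patients, random error is small, so a modest systematic shift may not be lost in noise.

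A second, lesser gap is that six months is shorter than a pregnancy, while Covariates item 7 speaks of the prenatal period without limiting it.

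**Working it through.** The Protocol gives no figure on this point, so there is none to reproduce.

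**Inputs from the Protocol:** a six-month window (about 183 days, 26.1 weeks); a birth date as the only trigger; outcomes up to extraction.

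**Assumed inputs, not in the Protocol:** 40 weeks (280 days) of gestation; births spread evenly over time; an 18-month post-period (other lengths shown); 3–6% of measured women aged 20–39 in late pregnancy, meaning the 26 weeks the rule is meant to remove; 5–10 kg of pregnancy weight in those women.

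**1. Is the pre-period protected?** A reading on 1 March 2020 needs births visible to about 1 September 2020. The Protocol's web references were retrieved on 7 September 2021, so extraction comes later than that. The six-month window therefore works in full for the pre-period.

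**2. Early pregnancy left in, both periods.** 280 − 183 = 97 days = 13.9 weeks; 97/280 = 35% of the pregnancy. At 37 or 42 weeks' gestation it is about 11 or 16 weeks.

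**3. Leak from births not yet recorded, post-period only.** For a reading *t* weeks before extraction, the share of all pregnancy time that escapes is max(0, 26.09 − *t*)/40, on top of the 35% from step 2.

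| Weeks before extraction | Leak | Total pregnancy time retained |
|---|---|---|
| 26 | 0.2% | 35% |
| 20 | 15.2% | 50% |
| 13 | 32.7% | 67.5% |
| 0 | 65.2% | 100% |

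The leak is a ramp, so on average half of late-pregnancy time escapes over the tail. Averaged over the whole post-period, the share is (26.09/2)/78.3 = 17% for 18 months, 25% for 12, 12.5% for 24 and 8% for 36.

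**4. Size in women aged 20–39.**
- At extraction: 0.03 × 5 = 0.15 kg to 0.06 × 10 = 0.6 kg.
- Averaged over the tail, at half: 0.075–0.3 kg.
- Over 18 months: × 26.09/78.3 = 0.333, giving 0.025–0.1 kg.

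Simple halving leans high, because the women who still leak early in the tail are at earlier gestation and have gained less. With assumed gain curves (0.5–2 kg by about week 14, 10–15 kg by term), the tail mean is 0.35–0.37 of the value at extraction (0.0120/0.0342; 0.1034/0.2772). That gives about 0.15 × 0.35 = 0.05 kg to 0.6 × 0.37 = 0.22 kg over the tail.

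**5. Size over all measurements.** With the same curves and 1–5% of all measurements from pregnant women (also assumed), mean weight rises by 0.03–0.28 kg at extraction, 0.01–0.10 kg over the last 26 weeks and 0.004–0.035 kg over 18 months. The early-pregnancy gap of step 2 adds 0.001–0.017 kg in each period.

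**6. Would a longer window be enough?** A 40-week window removes the 14-week gap, but births not yet recorded would then matter for readings up to 40 weeks before extraction instead of 26. It cannot stand alone.

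**The case against.** The strongest defence is that item 10 promises only to reduce pregnancy effects, that one rule applies in both periods, and that Covariates item 7 states the purpose of a variable without defining the prenatal period. On that view the six-month window is a reasonable working choice. Much of this stands, and it limits the point in several ways.

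- A reader might infer that both gaps inflate weight in the post-period only. They do not. The uncovered early weeks are retained before and after March 2020 and cancel to first order. Exact cancellation needs a stable share of readings from pregnant women, and the Protocol's section on risk of bias warns that who is measured may have changed.
- A reader might call the exclusion complete for the pre-period. That is true of the six-month window, not of the pregnancy as a whole.
- A reader might take the failure to reach back nine months. Under the current window it reaches six.
- The Protocol lists age and sex as separate covariates and does not define women of childbearing age as a stratum. In a stratum by age alone or sex alone the effect is diluted.
- Nothing in the Protocol supports a direction for blood pressure or lipids, so the point is confined to weight and BMI.

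The defence does not answer the unrecorded births. An aim of reducing pregnancy effects does not justify an avoidable difference between the two periods being compared.

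**Conclusion.** The point holds in a limited form. Followed as written, the rule lets late-pregnancy weights into about the last six months before extraction and into no comparable part of the pre-period. That mechanism follows from the Protocol's text; its size does not, since pregnancy share, weight gain and follow-up length are all assumed. On those assumptions the bias in women aged 20–39 is roughly 0.08–0.3 kg over the tail and about 0.03–0.1 kg over 18 months, and probably lower given the timing of weight gain. It would be larger if pregnant women are weighed more often than assumed, and smaller over a longer post-period. For adults as a whole it is slight.

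The main risk is a spurious late upturn in one demographic group, not a distorted overall result. The mismatch between item 10 and Covariates item 7 is a lesser matter of consistency. The change is a cheap improvement and worth making before the analysis.

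**What to change.** 1. Add a code list for current pregnancy. Exclude readings from the coded pregnancy until six months after it ends, with the same rule in both periods, alongside the birth-date rule. This also covers coded pregnancies that end without a registered birth.
2. Reconcile item 10 with Covariates item 7 by extending the pre-birth window to the full pregnancy, about 40 weeks. Do this only together with step 1, for the reason in step 6 of the working.
3. As a sensitivity analysis, drop the last window-length of follow-up before extraction for women of childbearing age.

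**Cost:** one extra code list, in a study that already plans to develop them, and the loss of some readings in women of childbearing age. Step 3 should stay a sensitivity analysis. At 40 weeks it removes 280 of about 548 days, or 51% of an 18-month post-period (38% of 24 months), and gives one group a different end of follow-up from the groups it is compared with.
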